### Data collectors

All the investigators will be in charge of the prospective data collection. The investigators are consultant and resident staff of the Department of Neurosciences, College of Medicine and Philippine General Hospital, University of the Philippines Manila.

### Data analysis plan

Descriptive statistics (mean, median, mode) of the numerical and nominal data will be obtained. Parametric tests will be used when our data follow normal distribution, otherwise, nonparametric test (Kruskal-Wallis test) will be used to compare the groups. The means of the 2 observer-masked scores pre-operative, 2 weeks, 3 months, 6 months, 9 months, and 12 months will be compared using a one-way analysis of covariance. A paired t-test will be done for the secondary endpoints: MoCA, EQ-5D-5L, and the nonmotor portion of the XDP-MDSP Scale. P-values of < 0.05 will be considered statistically significant. An interim analysis will be performed at either the 6-month timepoint or when 50% of patients have been enrolled, whichever comes first.

Protocol registration and technical review approval

This protocol was registered in the ClinicalTrials.gov website (Trial registration number: NCT05592028). It has received technical review board approval from the Department of Neurosciences, College of Medicine and Philippine General Hospital, University of the Philippines Manila.

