### Setting and participants

The study will be conducted at the PGH, Manila, Philippines. Adult XDP patients aged between 18–65 will be recruited for this study. All participants will undergo MRgFUS pallidothalamic tractotomy. Based on the list of patients as of December 2022, there are approximately 30 XDP patients who have sought consult at the PGH within the past 4 years.

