### Study procedure

Between 2023 and 2026, all adult patients with XDP fulfilling the inclusion criteria for MRgFUS pallidothalamic tractotomy will be invited to participate in the study. The patient’s written, informed consent will be secured on hospital admission for the procedure.

The procedure will be performed by one of the investigators ([name]) inside the MR imaging (MRI) suite, using a 1.5 Tesla MRI system (GE Optima MR450, USA) and the ExAblate Neuro device (InSightec, Haifa, Israel) to deliver the focused ultrasound. The patient’s head will be shaved and immobilized using a stereotactic frame under local anesthesia. An elastic diaphragm will be attached to the patient’s head and connected to the ultrasound transducer, and the patient will be positioned inside the bore of the MRI. A reference MRI scan will be performed to position the transducer to the target, after which the MRI images (T1-weighted axial and T2-weighted axial/coronal MRI at 1 mm slices) will be fused to the preoperative CT scan for the skull-correction algorithm. Stereotactic treatment planning will then be performed to target the PTT. It is usually located at the midcommisural line (0 to 1.0 mm posterior) in the anterior-posterior direction, 8–10 mm lateral to the intercommisural line in the mediolateral direction, 0-1.5 mm inferior to the intercommisural line in the dorsoventral direction, and 6.5–7.5 mm to the thalamo-ventricular border [18]. The lesion will be made 3 mm lateral to the mamillo-thalamic tract and superior and medial to the medial subthalamic nucleus [16, 19, 20]. Once the target is set, a series of low-power sonications producing temperatures between 40-45^o^C and lasting 10–20 seconds will be performed. Clinical assessment for improvement and treatment side effects will be made after each sonication, and definitive non-reversible thermal ablation will be performed only at the setting wherein the patient experiences tremor reduction or suppression or improvement of the dystonia with no adverse effects. The final sonication temperature usually ranges between 55-63^o^C. After the treatment, the stereotactic frame will be removed and the patient will be monitored in the hospital overnight.

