The patients will be assessed within 24 hours of treatment then asked to follow up with the movement disorder neurologist ([name]) at 2 weeks, 3 months, 6 months, 9 months, and 12 months post-treatment through a clinic visit. A written and standardized video protocol for the movement exam will be presented to all participants which will show the rating scales such as XDP-MDSP Scale, BFMDRS, and Movement Disorder Society-Unified Parkinson’s disease Rating Scale (MDS-UPDRS). Video recording will be taken at the initial visit and at each of the follow-up visits. Another blinded assessor, who is not connected with the PGH, will be asked to score the videos of the patients. The primary outcome will be assessed using the XDP-MDSP Scale, BFMDRS, and MDS-UPDRS at each visit, which will then be compared to the pre-treatment baseline recordings. In addition, XDP clinical and functional stage will be assessed [1]. Adverse effects, including skin burn, headache, arm or leg pain, muscle weakness, paresthesia, and unsteady gait, will be monitored at every follow-up.

For patients who have previously undergone a unilateral MRgFUS pallidothalamic tractotomy, the contralateral lesion will be performed at 12 months following the first procedure, provided that there are no serious adverse effects from the first PTT lesioning.

Moreover, we will also look into the: (a) demographic and clinical profile, (b) neuroimaging findings (cranial computed tomography and MRI), (c) MRgFUS treatment parameters (number of sonications, maximum energy, maximum temperature, duration of treatment), (d) change in the non-motor features using the XDP-MDSP Scale, (e) change in the XDP clinical and functional stage, (f) change in the BFMDRS and the part III of the MDS-UPDRS, (g) to determine the improvement in the patient’s quality of life using the five-level EuroQol five-dimensional questionnaire (EQ-5D-5L) at baseline, 3 months, 6 months, 9 months, and 12 months, (h) Montreal Cognitive Assessment (MoCA) (English, Pilipino, or Hiligaynon versions) at baseline, 6 months, and 12 months, and (i) to determine the safety of unilateral and staged bilateral MRgFUS procedure (see supplementary material 2).

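### The primary comparison is said to rest on two masked scores, but the only second assessor described is the clinic neurologist, who cannot be masked to before versus after treatment

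*Protocol article*

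**What the plan says.** The Data analysis plan compares "The means of the 2 observer-masked scores" at baseline, at 2 weeks and at 3, 6, 9 and 12 months, by a one-way analysis of covariance. It does not say who the two observers are.

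The Study procedure section states: "The primary outcome will be assessed using the XDP-MDSP Scale, BFMDRS, and MDS-UPDRS at each visit", against the pre-treatment recordings. It mentions two people who could supply these scores. Patients are "asked to follow up with the movement disorder neurologist" in clinic at 2 weeks and at 3, 6, 9 and 12 months. Video is taken at the initial visit and at each follow-up visit, and then: "Another blinded assessor, who is not connected with the PGH, will be asked to score the videos of the patients".

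The design has one arm. Setting and participants states: "All participants will undergo MRgFUS pallidothalamic tractotomy".

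Two further items bear on the point. The Data analysis plan makes the nonmotor portion of the XDP-MDSP Scale a secondary endpoint with its own paired t-test. It also schedules an interim analysis at the 6-month timepoint or at 50% enrolment, whichever is earlier.

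**The concern.** With no control arm, masked rating is the main stated safeguard against raters seeing the improvement they expect. The plan calls both scores masked, yet its visit procedure describes only one assessor who could be. If the clinic neurologist supplies the other score, the plan claims more protection than it has, and readers of the results would take the primary estimate as fully masked when part of it is not.

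The bias would also run in one direction. A rater who knows that the lesion has been made and hopes for benefit will tend to score later visits as better. A larger sample does not remove such a shift; it makes the shift more likely to reach significance.

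**Working it through.** The documents give no figure for rater bias or rater agreement, so there is no stated number to reproduce. The check sets the sections side by side and then works out how much of one rater's bias would pass through.

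**1. Who the two observers can be.** The Data analysis plan needs two masked scores per time point. Study procedure names a clinic neurologist and then introduces the video scorer as another blinded assessor. That wording counts a first assessor as already blinded, and the neurologist is the only other assessor described. This makes the neurologist the natural reading for the first observer, but it remains an inference.

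**2. What can be masked.** All participants are treated, so there is no allocation to hide. What remains is whether an assessment is before or after treatment. A clinician who sees the patient in person at a scheduled follow-up, where adverse effects are also checked, knows this. A video assessor can be kept from knowing it if the recordings do not reveal it. For early recordings one cue stands in the text: the patient's "head will be shaved and immobilized using a stereotactic frame under local anesthesia".

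**3. Share of bias that enters.** Let b be the neurologist's own bias in the change score and c the video rater's. For an equal-weight mean, bias = (b + c)/2.

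| c as a share of b | Bias of the mean, as a share of b |
|---|---|
| 0 | 0.50 |
| 0.25 | 0.625 |
| 0.50 | 0.75 |
| 1 | 1.00 |

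One half is therefore the value when the video rater is unbiased. It rises if that rater can also tell the visit.

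**4. Illustration on the scale of the expected effect.** The Introduction cites improvements of 30–36% in four earlier patients, midpoint 33%. With b assumed to be 5 to 15 percentage points and c = 0, the mean carries 2.5 to 7.5 points: 2.5/33 = 8% and 7.5/33 = 23% of that midpoint.

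**5. Illustration on the false-positive rate.** Assume no true change, c = 0, b in SDs of one rater's change score, inter-rater correlation r, and a two-sided 0.05 z-test of mean change (sidedness is not stated, and this is simpler than the planned model). The averaged change has SD √((1 + r)/2), so the test statistic is centred at e = (b/2)·√n / √((1 + r)/2), and P(significant) = 1 − Φ(1.96 − e) + Φ(−1.96 − e). The sample sizes are the ends of the protocol's range, 28 and 70.

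| b (assumed) | n = 28, r = 0.9 to 0.7 | n = 70, r = 0.9 to 0.7 |
|---|---|---|
| 0.2 | 0.084–0.089 | 0.138–0.148 |
| 0.4 | 0.192–0.209 | 0.404–0.442 |
| 0.6 | 0.370–0.406 | 0.731–0.777 |

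For example, with n = 28, b = 0.4 and r = 0.7: e = 0.2 × 5.29/0.922 = 1.15, giving 0.209 against a nominal 0.05.

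**6. What the two observers score.** Study procedure names the whole XDP-MDSP Scale for the primary outcome, while the Data analysis plan moves its nonmotor portion to a secondary endpoint. The masked comparison can be read as motor-only, but the text does not say so.

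**The case against.** The strongest reply is that the protocol never says the neurologist is one of the two observers. Patients follow up with that clinician, but the first blinded assessor could be a second video rater whom a condensed article does not describe. The means could also be group means at each time point rather than an average of two raters within a patient. Both points stand. They make the finding conditional, but they do not remove the need to say who the two masked observers are.

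A reader might go further and infer that half of any expectation bias enters the primary result. The documents do not support that. One half applies only to the clinic rater's own bias, with equal weights and an unbiased video rater. Patients' own expectation affects how they perform, is captured on video, and passes through both scores.

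A reader might also infer that the video rater is unmasked. The text does not show it. The shaved head concerns early recordings only, and the article's silence on labels and viewing order is a detail that a full protocol may settle. Nor does the statement "All the investigators will be in charge of the prospective data collection" establish that investigators rate the primary outcome.

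Finally, if two masked video raters do exist, cutting to one would lose precision and a real safeguard. That is right, and the fix allows for it.

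**Conclusion.** The point holds in conditional form. The primary comparison is labelled as resting on two masked scores, but the protocol describes only one assessor who could be masked to before versus after treatment. If the clinic neurologist is the other observer, the label is wrong for that rater, and that rater's bias enters the primary result: b/2 under equal-weight averaging with an unbiased video rater, more if the video rater can tell the visit.

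The size of b is unknown. The 8–23% and the inflated false-positive rates show what assumed values would do and are not estimates for this trial; the 30–36% benchmark itself comes from four patients. The conclusion rests on two inferences, the neurologist's role and within-patient averaging. The first is strong; the second affects only the share. It deserves settling before scoring starts, because no other comparison in this single-arm design would reveal rater bias.

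**What to change.** Name the role of each observer in the Data analysis plan, and make these changes:

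- Base the primary analysis only on video scores of the motor items, given by raters masked to visit.
- Strip visit and date labels from baseline and follow-up videos, show them in random order, and cover the scalp in every recording, baseline included.
- Score in randomised batches that mix baseline and follow-up videos, with one batch completed before the interim analysis. A single batch at the end of the study could not supply masked scores for that analysis.
- Report the clinic neurologist's scores as secondary, with inter-rater agreement.
- Apply the word masked only to the video rater or raters. If a second masked video rater exists, state that role and keep the two-rater mean.

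The cost is a video-handling instruction and a few sentences in the analysis section, using the same raters and recordings. If only one masked rater remains, the primary score is somewhat noisier than a mean of two, and scoring has to wait for each batch.

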### Sample size

The sample size for this study was computed to range between 28 and 70 participants (see Table 1), with an expectation of a medium or large effect, using repeated measures Analysis of Variance (RM-ANOVA) for within-subject comparisons (as measures are taken 3 times per patient). To compute for the sample, the wp.rmanova function from WebPower package was used [24].

**Table 1 Tab1:** Sample Size Computations

F value	Minimum Sample (n*)	Inflated Sample Formula: n* / (1-DOR)
0.25 (Medium Effect)	62.5	69.5
0.30	43.5	48.5
0.35	32.5	36
0.40 (Large Effect)	24.5	27.5

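### The visit scores of a single treated cohort are to be compared by independent-samples tests (one-way ANCOVA, or Kruskal-Wallis), although the sample size assumes a within-subject RM-ANOVA

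*Protocol article*

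**What the plan says.** The design has one cohort. Setting and participants states: "All participants will undergo MRgFUS pallidothalamic tractotomy". Study procedure says that the primary outcome is assessed on three scales at each visit, "which will then be compared to the pre-treatment baseline recordings". The question is therefore change within patients.

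The Data analysis plan lists six time points (pre-operative, 2 weeks, 3, 6, 9 and 12 months) and says that the mean observer-masked scores at 2 weeks, 3, 6, 9 "and 12 months will be compared using a one-way analysis of covariance", along with the pre-operative mean. No covariate and no patient effect is named. If the data are not normal, "otherwise, nonparametric test (Kruskal-Wallis test) will be used to compare the groups". In the same paragraph: "A paired t-test will be done for the secondary endpoints", and "P-values of < 0.05 will be considered statistically significant".

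The Sample size section computes the number of patients "using repeated measures Analysis of Variance (RM-ANOVA) for within-subject comparisons", on the footing that measures are taken three times per patient.

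**The concern.** A one-way analysis, with or without a covariate, and the Kruskal-Wallis test both take the compared sets of scores to come from different, independent patients. Here the same patients supply all six sets. Stable differences between patients, which cancel when a patient is compared with himself, then remain in the error term.

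The protocol is also inconsistent. It sizes the trial on a within-subject test with three measures, analyses six time points with a between-subject test, and uses a paired test only for the secondary endpoints.

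Two things are at stake. The objective is to estimate efficacy, and the intervals around change from baseline would be wrong. And the disease is rare: the article counts about 30 patients seen at the site in four years, so the sample may sit near the low end of the planned 28 to 70, where within-patient information matters most.

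**Working it through.** **Inputs from the article:** one cohort; six time points; alpha 0.05; n = 25, from the bottom row of Table 1 (24.5, rounded up).

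**Inputs assumed, because the article does not give them:** within-patient correlation rho (0.3 to 0.7), equal between all visits; normal scores with SD 1; the same shift d (in SD) at all five follow-up visits. As no covariate is named, the one-way test is taken without one.

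**Table 1.** Its figures cannot be reproduced from stated inputs, because power, dropout rate, number of groups and correlation are not given. The inflation column fits a dropout of about 10% (62.5/0.9 = 69.4, printed as 69.5). Table 1 serves here only as the source of n.

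**Step 1: standard error of a visit contrast.**
- Independent samples: sqrt(2 SD²/n).
- Same patients: sqrt(2 SD²(1 - rho)/n).
- Ratio: 1/sqrt(1 - rho).
 - rho 0.3: 1/sqrt(0.7) = 1.20
 - rho 0.5: 1/sqrt(0.5) = 1.41
 - rho 0.7: 1/sqrt(0.3) = 1.83

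**Step 2: rejection rate with no effect (nominal 5%).** By simulation, the one-way F test rejects 4.9% at rho 0, 0.9% at rho 0.3, 0.1% at rho 0.5 and about 0% at rho 0.7. RM-ANOVA stays at about 5%. At rho 0.5 Kruskal-Wallis rejects 0.05% and Friedman 5.6%.

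**Step 3: power.** For RM-ANOVA the noncentrality is lambda = n × d² × (5/6)/(1 - rho), with 5 and 120 degrees of freedom. For rho 0.5 and d 0.5: 25 × 0.25 × 0.833/0.5 = 10.4, which gives 67%. For rho 0.7 and d 0.4: 25 × 0.16 × 0.833/0.3 = 11.1, which gives 71% (72% in a simulation of 4,000 trials). One-way power is by simulation.

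| rho | shift d (SD) | one-way | RM-ANOVA |
|---|---|---|---|
| 0.3 | 0.5 | 26% | 51% |
| 0.5 | 0.5 | 18% | 67% |
| 0.7 | 0.4 | 3% | 71% |
| 0.5 | 0.67 | 51% | 93% |
| 0.7 | 0.67 | 44% | 99% |
| 0.5 to 0.7 | 1.07 | 99% | about 100% |

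At rho 0.7 and 0.4 SD, Kruskal-Wallis has about 2% power and Friedman 61%.

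**Step 4: sphericity.** If the correlation decays over visits (autoregressive, 0.7 between neighbours), uncorrected RM-ANOVA rejects 7.5% under no effect. A replacement RM-ANOVA therefore needs a correction.

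**Step 5: the covariate.** If the pre-operative score were the covariate, it could not also be one of the compared means. With it removed from them, the visit test would compare follow-up visits with each other and not with baseline.

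**The case against.** The strongest reply is that the power loss may not matter at the effects the trial expects. If the F value in Table 1 is the between-visit SD over the total SD, a shift d at five of six visits gives f = d × sqrt(5)/6. The 0.4 SD case is then f = 0.15, below Table 1's smallest value of 0.25. The row with about 25 patients assumes f = 0.40, or d = 1.07, where the one-way test has about 99% power. With f = 0.25 (d = 0.67) and 63 patients it also has 99% or more. This stands, with the caveat that the article does not define f and another definition would imply smaller shifts. A reader might infer that most of the power is lost; the documents do not support that without conditions.

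Other strong readings also fail:
- A reader might fear false positives. With positive correlation the stated tests err the other way. Inflation would arise if follow-up changes were pooled as independent values, but the article plans no such analysis.
- Baseline as covariate is a supposition, since the text names none.
- Kruskal-Wallis is said to compare groups, which are not defined. Visits are the natural reading, but the article also distinguishes unilateral from staged bilateral treatment.
- The Data analysis plan does not call the ANCOVA primary. That follows from Study procedure, which makes these scales the primary outcome.

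A separate analysis plan may exist, but it would not remove the point: the article does not leave the test open, it names one that does not fit the design.

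**Conclusion.** The point holds as a wrongly stated method and an internal contradiction. The test named for the primary-outcome scores ignores that all six sets come from the same patients, as does its fallback if it compares visits, and the ANCOVA disagrees with the sample size section in both test and number of measures (three against six).

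With positive within-patient correlation the p-values are too large and the standard errors of change from baseline are inflated by about 1.2 to 1.8 times for rho 0.3 to 0.7. The risk is a missed or imprecisely estimated benefit, not a false claim. At n = 25 the power loss runs from negligible (about 1 SD) to nearly complete (rho 0.7, 0.4 SD). Where in that range the trial lies cannot be settled from the article, which gives neither correlation nor SD. The interval error remains even where power is ample, and bears directly on the objective to estimate efficacy.

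**What to change.** In the Data analysis plan, replace the one-way ANCOVA with one repeated-measures analysis. Either of these would serve:
- a linear mixed model with the scores at all six visits, baseline included, as outcomes; visit as a categorical fixed effect; and a within-patient covariance that about 25 patients can support (an unstructured one has 6 × 7/2 = 21 parameters, so name a simpler alternative in advance);
- RM-ANOVA with a sphericity correction, which stays closest to the Sample size section.

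Report change from baseline at each visit with its 95% confidence interval. Replace Kruskal-Wallis with the Friedman test, or with Wilcoxon signed-rank tests on change from baseline. If Kruskal-Wallis was meant for some other comparison, name its groups.

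In the Sample size section, use the same model and the same number of visits, state power, dropout and assumed correlation, and restate Table 1 if its figures change. The paired t-tests for the secondary endpoints may stay, since they respect the pairing.

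The cost is rewording and one recalculation; no new data or visits are needed.

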## Discussion

Recent advances in medical technology, including MRgFUS, have shown promise in the field of neurosurgery [19]. MRgFUS is an innovative, non-invasive surgical technique that combines the precision of MRI imaging with the therapeutic potential of focused ultrasound waves. Furthermore, MRgFUS has shown efficacy in various neurosurgical procedures, including the treatment of ET and PD [19, 20]. Pallidothalamic tractotomy involves the precise destruction of specific neural pathways involved in movement regulation, particularly the connections between the globus pallidus and the thalamus [19]. By using MRgFUS, neurosurgeons can perform this procedure without making any incisions, minimizing the risk of complications associated with traditional surgical interventions [19]. Therefore, the advantages of using MRgFUS include an improved safety profile, enhanced precision and targeting, and minimal invasiveness, improving recovery times [19, 20].

Conducting a study on MRgFUS pallidothalamic tractotomy for patients with XDP holds great promise for improving patient outcomes. By selectively ablating specific neural pathways involved in movement regulation, this novel technique has the potential to alleviate motor symptoms, reduce dystonia, and improve overall motor function. Such improvements would significantly enhance the quality of life for individuals living with XDP, allowing them to regain independence and engage in daily activities.

